### Outcome Measure Assessment

The outcome measures assessed include mental and physical fatigue, overall cognitive condition, attention, working memory, sleep quality, and resting-state MRI scans. Primary and secondary outcomes, along with related self-assessment scale measurements such as the MFI-20, Montreal Cognitive Assessment (MoCA), Attention Network Test (ANT), and Working Memory Test (N-Back), will be assessed at baseline (week 1), at the end of the intervention (week 13), and at follow-up (week 18). Table 1 presents the detailed outcome assessment time points.

**Table 1 table1:** Outline and timelines of the assessments.

Time points	Baseline (week 1)	Intervention period (weeks 2-13)	Postintervention (week 14)	Follow-up (week 18)
Inclusion criteria	✓	N/A^a^	N/A	N/A
Exclusion criteria	✓	N/A	N/A	N/A
Informed consent	✓	N/A	N/A	N/A
Randomization and allocation	✓	N/A	N/A	N/A
Intervention	N/A	✓	✓	N/A
20-item Multi-Dimensional Fatigue Inventory	✓	N/A	✓	✓
Montreal Cognitive Assessment	✓	N/A	✓	✓
Attention Network Test	✓	N/A	✓	✓
Working Memory Test (N-Back)	✓	N/A	✓	✓
Pittsburgh Sleep Quality Index	✓	N/A	✓	✓
Amplitude of low-frequency fluctuation	✓	N/A	✓	N/A
Functional connectivity	✓	N/A	✓	N/A
Adverse events	N/A	✓	✓	✓

^a^N/A: not applicable.

### Demographic and Clinical Characteristics of the Participants

The researchers will collect data on the demographic characteristics of the participants (such as age, sex, education level, marital status, living arrangements, occupation, and socioeconomic status), as well as their medical and medication history using a self-designed questionnaire. Baseline assessments will be completed before randomization.

### Primary Outcome Measure

#### MFI-20

The MFI-20 scale was developed by Smets et al [30] in 1995, after validation with patients undergoing cancer radiotherapy, individuals with CFS, psychology students, medical students, doctors, and recruits. The scale consists of 20 items, which are grouped into 5 dimensions: general fatigue, physical fatigue, reduced activity, reduced motivation, and mental fatigue. To minimize bias toward a particular direction, each dimension includes 2 statements about fatigue and 2 about the opposite (ie, not fatigued), making up a total of 4 items. Each item is scored using a 5-point Likert scale, where 1 point indicates “completely disagree” and 5 points indicate “completely agree,” resulting in a total score range of 20-100. Among these, items 2, 5, 9, 10, 13, 14, 16, 17, 18, and 19 are positively scored to reflect fatigue. Items 1, 3, 4, 6, 7, 8, 11, 12, 15, and 20 are scored inversely, reflecting the absence of fatigue. A higher score indicates more severe fatigue symptoms [31].

### Secondary Outcome Measures

#### MoCA

The MoCA scale is used to assess general cognitive status and overcomes the low sensitivity of other cognitive assessment tools to cognitive impairment. It is one of the most widely used cognitive assessment tools in clinical practice and effectively screens for cognitive dysfunction caused by various diseases, especially with high sensitivity in the early stages. It covers a wide range of cognitive domains, including orientation, attention, language, visuospatial function, memory, and executive functions. The total score is 30, with a score of 26 or higher considered normal. Scores are slightly adjusted based on educational level; for example, participants with less than 12 years of education receive an additional point added to their final MoCA score.

#### ANT

The behavioral measurement of attention is conducted using the ANT protocol proposed by Fan et al [32]. This test is administered on a computer using the E-Prime 3.0 software (Psychology Software Tools, Inc.), where stimuli are presented, and the participants’ keypress responses and reaction times for all trials are recorded. ANT measures 3 distinct attention networks: alerting, orienting, and executive control. It includes 2 main operational variables: cue type and target stimulus type. Cue types are divided into no cue, neutral cue, and spatial cue. The target stimulus types are categorized into congruent and incongruent stimuli.

The experimental stimuli consist of 3 types of original materials: the cue stimulus (“”), the target stimulus arrow (either “→” or “←”), and the fixation point (“+”). Each trial begins with a phase where the “+” fixation point appears at the center of the screen for approximately 400-1600 ms. This is followed by the cue stimulus (“”), which appears in 1 of 4 forms for approximately 100 ms. After the cue signal disappears, the fixation point (“+”) reappears alone for approximately 400 ms. Following this, the target stimulus is displayed either above or below the fixation point and remains on the screen until the participant responds. The participant’s reaction time must be less than 1700 ms. After the participant presses a key within the allotted time, the target stimulus disappears, and the fixation point (“+”) reappears in the center of the screen, signaling the start of the next trial. Each trial lasts less than 4000 ms. The cue stimulus (the asterisk “*”) can be in 1 of 4 states based on its presence and location: no cue, double cue, spatial cue, and center cue. No cue indicates that only the fixation point is displayed. The double cue indicates that asterisks appear simultaneously above and below the fixation point. The spatial cue indicates that an asterisk appears just below or above the fixation point. The center cue indicates that the asterisk is positioned in the center of the screen, replacing the fixation point. The target stimulus is a gray arrow displayed on the screen, flanked by 2 arrows on each side. These arrows may point in the same direction as the target arrow (congruent condition), in the opposite direction (incongruent condition), or be replaced by short lines (neutral condition).

In the experimental condition, participants are required to place their hands on the keyboard and focus their eyes on the fixation point in the center of the computer monitor. They must make a fast and accurate autonomous response based on the direction of the target stimulus. Specifically, if the central arrow of the target stimulus points left, participants are instructed to press the “F” key. If the central arrow points right, they should press the “J” key. The software automatically records the participant’s accuracy and reaction time. The task begins with 24 practice trials, followed by the formal experiment, which is divided into 3 blocks, each containing 96 trials. Participants are allowed to rest appropriately between blocks and can start the next block by pressing the space bar on the keyboard. The distribution of cue stimuli and target stimuli is balanced to ensure equal representation across trial types. The total duration of the task is approximately 30 minutes. The behavioral metrics include accuracy rate (higher is better), reaction time (faster is better), alerting score (no-cue reaction time [RT] to neutral-cue RT), orienting score (neutral-cue RT to spatial-cue RT), and conflict score (incongruent RT to congruent RT).

#### N-Back Test

This study uses the N-Back task paradigm to assess working memory, one of the classic experimental approaches for evaluating this cognitive function. The task is implemented using E-Prime 3.0 software and is performed on a computer with a keyboard. It presents stimuli and records participants’ reaction times and accuracy rates across all trials. During the test, participants are required to sit in front of the computer screen, maintaining a horizontal distance of 60 cm. The index fingers of the participant’s left and right hands should lightly touch the F and J keys on the keyboard, ready to respond by pressing a key when a letter appears. The N-Back paradigm includes 3 levels of memory load (0=back, 1=back, and 2=back tasks), with stimuli consisting of the letters A, B, C, D, E, and F against a black screen background with white letters. At the start of the experiment, a “+” is first displayed for 500 ms, followed by the random presentation of English letters. Each stimulus is presented for 500 ms, with an interstimulus interval of 2000 ms (blank screen). If no response is made within 2000 ms, the next stimulus is automatically presented. After each block, a prompt message saying, “Please rest for a moment; press the space bar to continue” appears. In the 0=back task, participants are instructed to compare the current letter with “X” and press the F key if they are the same or the J key if they are different. In the 1=back task, starting from the second letter, participants are instructed to determine whether the current letter is the same as the previous letter, pressing the F key if they are the same or the J key if they are different. In the 2=back task, starting from the third letter, participants are instructed to determine whether the current letter is the same as the letter 2 positions back, pressing the F key if they are the same or the J key if they are different. Participants are required to respond both quickly and accurately. The task includes 60 practice trials, followed by the formal experiment, which consists of 9 blocks, each with 30 trials (15 targets and 15 nontargets). Each memory load level includes 3 blocks, with the 0=back, 1=back, and 2=back tasks completed in sequence. Each task type involves a total of 90 stimuli (30 × 3), with a target-to-nontarget ratio of 1:1, presented in a pseudorandom order. The behavioral metrics include reaction time and accuracy rate.

In the sequence of conducting the ANT and N-Back tests, the ANT test lasts for 30 minutes, followed by the N-Back test, which lasts 15 minutes. The tests are administered consecutively, with a structured break in between. Specifically, after completing the N-Back test, participants are given a 5-minute rest period before proceeding with the ANT test. This design ensures a smooth transition while allowing participants to briefly recuperate, minimizing cognitive fatigue and maintaining optimal performance throughout the testing process. By balancing test durations and incorporating rest intervals, this approach facilitates a more reliable assessment of cognitive abilities.

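### The 0-back target letter X is not in the stated A–F stimulus set, and the ANT alerting and orienting scores rest on a neutral cue that is never mapped to the cues shown

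*Protocol article*

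**What the plan says.** **N-Back Test section.** The paradigm has three loads (0-, 1- and 2-back), "with stimuli consisting of the letters A, B, C, D, E, and F against a black screen background with white letters". No separate letter set is given for any load. In the 0-back task, "participants are instructed to compare the current letter with" X, using the F key for same and the J key for different. The formal experiment is one "which consists of 9 blocks, each with 30 trials (15 targets and 15 nontargets"). The section then adds: "Each task type involves a total of 90 stimuli (30 × 3), with a target-to-nontarget ratio of 1:1". In the 1-back task, participants "determine whether the current letter is the same as the previous letter"; the 2-back task looks two letters back. The metrics are reaction time (RT) and accuracy.

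**ANT section.** The section first lists three cue types: none, neutral and spatial. It then describes the cue actually displayed as being in one of four states: "no cue, double cue, spatial cue, and center cue". The only displayed condition it labels neutral is a flanker condition, in which short lines replace the flanking arrows; that is not a cue. The scores are given as "alerting score (no-cue reaction time [RT] to neutral-cue RT), orienting score (neutral-cue RT to spatial-cue RT"), followed by a conflict score from incongruent and congruent RTs. There are 3 blocks of 96 trials, with cue and target types balanced.

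**Statistical Analysis section.** ANT and N-Back metrics go into a 2 (group) × 2 (time) repeated measures ANOVA.

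**The concern.** In the N-Back section, three statements cannot all be true: the letters are A to F, the 0-back target is X, and half of each block's trials are targets. If the task ran with A to F only, the 0-back level would contain nothing to detect. A participant who never looked at the screen could score perfectly, and RT to targets would not exist.

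In the ANT section, two of the three network scores are written in terms of a cue that is not among the displays as named. Someone must decide later which displays count as neutral, and if that is settled after results are seen, the definition can follow the data.

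This matters because participants are not blinded and the primary outcome is self-reported. The Discussion leans on these computerized tasks as its objective evidence on cognition.

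**Working it through.** **N-Back: the plan's own figures**

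- Inputs (N-Back Test section): 9 blocks, 3 loads, 30 trials and 15 targets per block.
- Blocks per load: 9 / 3 = 3.
- Stimuli per load: 3 × 30 = 90, which reproduces the stated 90.
- Targets per load: 3 × 15 = 45, with 90 − 45 = 45 nontargets, which reproduces the stated 1:1 ratio.
- Whole task: 9 × 30 = 270 trials and 9 × 15 = 135 targets.

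**N-Back: against the stated letters**

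- 0-back: a target is a trial showing X. X is not in {A, B, C, D, E, F}, so 0 of the 45 required targets can occur and the split is 0:90. Always pressing J gives 90/90 = 100% accuracy. Under the intended 45:45 split it would give 45/90 = 50%.
- 1-back and 2-back: a target is a repeat of an earlier letter. In a 30-letter block, 30 − 1 = 29 positions (1-back) or 30 − 2 = 28 positions (2-back) can hold a match, so 15 targets fit with six letters. Both levels work as written.

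**ANT: what neutral can mean**

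- Trials: 3 × 96 = 288. Four balanced cue states give 288 / 4 = 72 each.
- Removing the no-cue and spatial states leaves double and center. Neutral is therefore 72 trials (one of them) or 144 trials (both pooled).
- Block size does not show which description was programmed: 96 divides evenly by 3 × 2 = 6 cells (three cue types, two target types) and by 4 × 3 = 12 cells (four cue states, three target conditions).

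The documents give no RTs, so the effect on the scores can only be illustrated. Assume mean RTs of 600 ms (no cue), 550 (double), 570 (center) and 520 (spatial), with scores taken as differences:

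| Neutral taken as | Alerting (ms) | Orienting (ms) |
|---|---|---|
| double | 600 − 550 = 50 | 550 − 520 = 30 |
| center | 600 − 570 = 30 | 570 − 520 = 50 |
| both pooled (mean 560) | 600 − 560 = 40 | 560 − 520 = 40 |
| double for alerting, center for orienting | 50 | 50 |

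If double and center RTs differ by D ms, switching the definition moves each score by up to D. With D = 0 (both 560 ms) every row gives 40 and 40 and the choice is immaterial; with D = 20, as in the table, the scores move by up to 20 ms.

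For the planned group × time comparison, a D that is the same in both groups at both times cancels in expectation. The expected estimate then changes only if the groups' changes over time differ between double-cue and center-cue RT, although any one sample will still vary with the choice.

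The conflict score, accuracy and overall RT contain no neutral-cue term.

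**The case against.** The best defense of the N-Back text is that the slip lies in the letter list alone. The same section names X as the target, fixes a 1:1 ratio and elsewhere speaks of letters drawn at random from the English alphabet. All of that implies that X was shown, and the programmed task may well be correct. This stands as a reason to check the script first. It does not remove the contradiction, because the article cannot show which statement is wrong.

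For the ANT, the three cue types can be read as scoring categories and the four states as displays. Sorting four displays into three categories puts both double and center under neutral. The section also says the task follows a published ANT protocol, and an analysis plan that is not shown may hold the scoring rule. That is a fair reading, so the scores are ambiguous, not impossible. But the pooled reading is an inference: the parallel list of target types omits the neutral flanker, so these short lists are not reliably complete.

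A reader might infer more than the documents support:

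- **That the cognitive tasks as a whole cannot be scored.** The 1-back, the 2-back, ANT conflict, ANT accuracy and ANT RT are all scorable.
- **That the 0-back fault spoils the other loads because it is their reference.** No contrast against 0-back is defined, and the planned ANOVA has no load factor.
- **That a shared neutral term harms the analysis by correlating alerting with orienting.** No planned analysis relates the two scores to each other.
- **That using F as both a stimulus letter and a response key is an error.** It contradicts nothing in the text.

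**Conclusion.** The N-Back Test section contradicts itself on the 0-back level: with the stated letters, 0 of 45 targets can occur and a constant J response is fully correct. This affects one of three loads, or 90 of 270 trials. It is a statement about the text; whether participants saw an X cannot be determined from it.

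The ANT point is smaller. Alerting and orienting are not fixed until the neutral cue is mapped to double, center or both (72 or 144 of 288 trials, assuming the four-state balanced design). The wording also leaves unstated whether each score is a difference or a ratio. How far the choice matters depends on how much double-cue and center-cue RTs differ, which the documents do not give.

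Both faults concern secondary outcomes in a pilot. The MFI-20 primary outcome and the sample size do not depend on them. They are worth settling now because the Results section says that no analysis has been performed.

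**What to change.** 1. Check the E-Prime N-Back script as run, and correct the stated 0-back letter set or target so that the 1:1 ratio is attainable.
2. If the script showed no X, report that, and do not interpret 0-back accuracy or target RT. If accuracy is summarized across loads, leave the 0-back trials out.
3. Before unblinding, state which displayed cue or cues count as neutral in each ANT score, consistent with the script, and state that the scores are RT differences. Two examples are no cue minus double cue for alerting with center cue minus spatial cue for orienting, or double and center pooled in both scores. The first uses different cues in the two scores, whereas the present text uses one term for both, so it should be declared as a clarification of the definition.
4. Make the two lists of cue and target types in the ANT section agree.

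The cost is a script check and a few lines of text. If the scripts are already right, no retesting is needed.

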#### Pittsburgh Sleep Quality Index

The Pittsburgh Sleep Quality Index (PSQI) was developed in 1989 by Buysse and colleagues [33] at the Sleep and Chronobiology Center of the Department of Psychiatry at the University of Pittsburgh Medical Center. The reliability and validity of the scale have been evaluated in China, with results showing that the index has good empirical validity. The PSQI comprises 19 items, covering 7 dimensions: subjective sleep quality, sleep duration, sleep latency (the time it takes to fall asleep), sleep disturbances, sleep efficiency, use of sleeping medication, and daytime dysfunction. The scale uses a scoring method of 0, 1, 2, and 3, with scores accumulated across dimensions, yielding a range of 0-21 points. A higher score indicates poorer sleep quality. A PSQI score of 7 is used as the cutoff point, with a score of less than 7 indicating acceptable sleep quality and more than 7 indicating poor sleep quality.

### Adverse Events and Safety

Adverse events are any unfavorable and unintended signs (including abnormal laboratory findings), symptoms, or diseases associated with the study, regardless of whether they are related to the medication used. Several studies have shown that Tai Chi is a relatively safe method for treating various diseases, including hypertension, with no reports of serious adverse reactions. If unexpected adverse events occur, defined as any functional impairments caused by the intervention, such as headaches, dizziness or vertigo, head fullness, tinnitus, chest tightness, worsening shortness of breath, increased heartbeat or palpitations, muscle soreness or pain, excessive sweating, irritability, neurasthenia, hallucinations, paranoia, or psychological stress—whether or not related to the treatment—the nearest doctor will be promptly notified for assessment and initiation of treatment.

If a serious adverse reaction occurs, the researcher will report it to the principal investigator and the ethics committee to determine whether the participant should be withdrawn from the study and treatment. The researchers will make every effort to prevent and treat any harm that may arise from this study. If the expert committee believes that the adverse event is related to the Tai Chi treatment, the research team will cover the treatment costs and provide appropriate financial compensation for damages related to the trial.

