### CFS Diagnostic Criteria

The clinical diagnosis is based on the CFS diagnostic criteria published by the UK’s NICE in 2021 [27]. The criteria are as follows: (1) debilitating fatigue exacerbated by activity, not by excessive cognitive, physical, emotional, or social exertion, and not significantly alleviated by rest; (2) cognitive impairments (brain fog), including slow responsiveness, short-term memory issues, and difficulties with concentration or multitasking; (3) Postexertional malaise, with symptoms typically delayed for hours or days after activity and disproportionate to the activity, with extended recovery time, lasting for hours, days, weeks, or longer; and (4) unrefreshing sleep or sleep disturbances (or both), characterized by exhaustion upon waking, feelings of stiffness and flu-like symptoms, interrupted or shallow sleep, altered sleep patterns, or hypersomnia. All 4 symptoms must be present simultaneously and persist for at least 3 months, with other possible medical causes of fatigue ruled out. The inclusion, exclusion, and withdrawal, drop-out, and termination criteria are listed in Textbox 1.

The inclusion, exclusion, withdrawal, drop-out, and termination criteria.

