### Intervention

#### Tai Chi Group

The Tai Chi group will practice the 24-form Tai Chi, led by an instructor from Shanghai University of Traditional Chinese Medicine with at least 5 years of teaching experience. Throughout the intervention period, there will be 3 sessions per week: 2 offline classes at the Shanghai University of Traditional Chinese Medicine Sports Center and 1 self-practice session, guided online by the instructor. Each practice session lasts 60 minutes, beginning with 5 minutes of Tai Chi preexercise stretching, followed by 10 minutes of Tai Chi standing postures. The instructor will then introduce and demonstrate each movement, explain precautions, answer participants’ questions, and provide individual guidance, correcting their movements for the next 30 minutes. The session ends with 5 minutes of relaxation. For home self-practice sessions, the duration is 60 minutes, supervised via video in a WeChat group. After each practice session, a practice log will be provided, and participants will be required to fill it out. The entire treatment process lasts for 12 weeks.

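### The adverse-event section gives conflicting wording on cause and does not name postexertional worsening, which every participant has at entry and which the protocol describes as delayed after activity.

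*Protocol article*

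**What the plan says.** Adverse Events and Safety contains three statements that bear on cause.

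- **General definition.** "Adverse events are any unfavorable and unintended signs (including abnormal laboratory findings), symptoms, or diseases associated with the study", and this applies "regardless of whether they are related to the medication used".
- **Unexpected adverse events.** These are "defined as any functional impairments caused by the intervention, such as headaches, dizziness or vertigo, head fullness", followed by further examples. The same sentence then adds "whether or not related to the treatment". When such an event occurs, "the nearest doctor will be promptly notified for assessment and initiation of treatment".
- **Onward reporting.** "If a serious adverse reaction occurs, the researcher will report it to the principal investigator and the ethics committee". The report serves to decide whether the participant should be withdrawn.

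CFS Diagnostic Criteria lists as its third criterion "Postexertional malaise, with symptoms typically delayed for hours or days after activity and disproportionate to the activity". All four criteria must be present together, and meeting the diagnosis is an inclusion criterion (Textbox 1).

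The Tai Chi arm has 3 sessions of 60 minutes a week for 12 weeks. On the log, the article says: "After each practice session, a practice log will be provided, and participants will be required to fill it out". The health education arm also completes a log after each learning session. Table 1 schedules adverse events for the intervention period, the postintervention visit and the follow-up visit. The Abstract's objective names safety alongside efficacy.

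**The concern.** Two features of the section combine.

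First, someone recording an event cannot tell from the text whether a judgement of cause comes before or after the event is written down. If staff resolve that differently in the two arms, the counts are not comparable. A requirement that the intervention caused the event is easier to meet for an exercise class than for lectures and messages. It is also easy to set aside for a symptom that the disease itself produces.

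Second, the harm that the entry criteria make most foreseeable is not named as a safety outcome anywhere in the article. Everyone enrolled has a symptom that the protocol itself describes as following activity after a delay, and one arm is given regular activity.

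What is at stake is the safety conclusion. The trial is meant to inform larger trials. A low event count would reassure only if this harm had been looked for.

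**Working it through.** No figure in the plan bears on this point, so the check is mainly one of setting the text side by side.

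**1. Wording on cause.**

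| Statement | Position on cause |
|---|---|
| General definition | Set aside, but only for a medication; neither arm has a study drug |
| Unexpected adverse event, start of the sentence | Caused by the intervention |
| Unexpected adverse event, end of the sentence | Relatedness not required |
| Onward reporting | A serious *reaction*, a term that normally implies cause; the section defines only *events* |

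The second and third rows cannot both hold. The first does not settle the matter, because its waiver refers to something the trial does not give. The fourth uses a term that the section does not define.

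**2. Is postexertional worsening named?** The unexpected-event sentence gives 14 examples, counting each *or* pair as one. Grouped by type, 4 concern the head and ears (tinnitus, headaches, a feeling of fullness, dizziness), 3 the heart and breathing (palpitations, breathlessness, tightness of the chest), 2 the muscles and skin (sweating, soreness) and 5 the mental state (paranoia, hallucinations, stress, irritability, neurasthenia): 4 + 3 + 2 + 5 = 14. Postexertional malaise is not among them, and no other section names it as a safety outcome.

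**3. Who has the symptom, and how much activity is planned?** All participants have it by entry rule. Planned exposure in the Tai Chi arm is 3 × 12 = 36 sessions per person, and 30 × 36 = 1,080 sessions at full attendance.

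**4. Do other measures fill the gap?** Not demonstrably. The MFI-20 is taken at baseline, postintervention and follow-up, so a flare that starts and resolves between visits can be missed. The logs exist in both arms, but the article does not say that they ask about symptoms. Table 1 has an adverse-event row covering the right periods, but what enters it depends on the definitions in step 1.

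**5. What would a zero count be taken to mean?** As an illustration only, suppose 0 of 30 Tai Chi participants had a recorded event and all 30 were followed. The exact upper limit is 1 − 0.05^(1/30) = 9.5% (one-sided 95%) or 1 − 0.025^(1/30) = 11.6% (two-sided 95%). Such a limit describes postexertional worsening only if that worsening was recorded whenever it occurred.

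**The case against.** The strongest reply is that the opening definition governs. It takes in any unfavorable symptom, and its evident intent, despite the ill-fitting word *medication*, is to disregard cause. On that reading a flare is already an adverse event. The example list is open-ended and includes neighbouring symptoms such as muscle soreness and neurasthenia. The sentence with the causal wording triggers a call to a doctor; it does not say what is counted. Table 1 restricts adverse events neither by cause nor by arm. Detailed forms and prompts may be in the full protocol, which is not shown.

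Most of this stands, and it rules out several stronger readings that a reader might infer:

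- *That the rules count only events judged to be caused by Tai Chi.* The text is contradictory rather than restrictive, and the causal clause is not a counting rule.
- *That flares are excluded.* They are only unnamed.
- *That the session log is completed too early to see a delayed reaction.* The article does not say that the log is the adverse-event instrument. A log kept 3 times a week could also pick up a delayed symptom at the next entry.
- *That staff who know the allocation decide on cause.* The article says only that the researcher reports. It blinds managers, data collectors and outcome assessors, and refers the relatedness judgement for compensation to an expert committee.
- *That a stated number of flares will be missed.* The documents give neither a flare rate nor a capture rate.

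The reply does not remove the contradiction within one sentence, the unmatched term *reaction*, or the silence on the one symptom that the entry criteria guarantee. The last of these would be weak on its own in a condensed article. It matters here because unclear wording on cause makes a delayed baseline symptom easy to set down to the disease.

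**Conclusion.** The point holds as a defect of wording together with an inexpensive gap in ascertainment. Adverse Events and Safety contradicts itself on whether cause matters, waives cause in terms that do not fit the trial, and words its reporting route for a reaction where it has defined events. It does not say whether worsening of postexertional symptoms is recorded as a safety outcome.

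The consequence is a possibility, not a demonstrated loss: flares could go unrecorded or be attributed to the disease, and counts in the two arms could rest on different bases. Its size cannot be derived from the documents. The conclusion rests on the article as published; if the full protocol already specifies neutral recording and a postexertional item, only the article's wording needs correction. It should be dealt with because safety is a stated objective and the remedy is small.

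**What to change.** - Reconcile the statements on cause in Adverse Events and Safety so that adverse events are recorded on the same basis in both arms, with relatedness rated separately. Replace the reference to a medication with wording that fits the two interventions.
- Reconcile the term *serious adverse reaction* with the adverse-event definition. Because that report feeds decisions on withdrawal, the request is only that the passages agree; no trigger is proposed here.
- State that worsening of postexertional symptoms is recorded as a safety outcome. Collect it with one item that has the same recall window in both arms, for example weekly and again at the postintervention and follow-up visits, and tabulate it by arm. An item tied to the time since the last session would not serve: the Tai Chi arm meets 3 times a week, while the control arm has daily messages and a weekly lecture, so the recall windows would differ.

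The cost is an amendment to the wording, one extra item for participants, and higher reported event counts. No change to clinical management is proposed. As recruitment began in April 2024, the report should state the date from which the item was collected.
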